#### Secondary outcomes

We will assess five secondary outcomes related to SRH and mental health. Table 1 summarizes the secondary outcomes to be assessed. We will compare baseline and endline measures of these outcomes.

**Table 1 Tab1:** Secondary outcomes to be assessed

Domain	Secondary outcome	Measurement
SRH	SRH knowledge	To be measured using a series of questions assessing adolescent mother’s knowledge of HIV and its transmission, the menstrual cycle, and contraceptive methods
	Current contraceptive use	To be assessed using two questions assessing current use of a contraceptive method to delay or avoid getting pregnant and the type of method used
	Transactional sex	To be measured using a series of questions on self-reported exchange of sex for money, girl, rent, food, school fees, phone/airtime, clothes/shoe/beauty products, sanitary pads, and security
	Experience of sexual and gender-based violence	To be assessed using a series of questions adapted from the *WHO multi-country study on women’s health and domestic violence against women* [29]
Mental health	Mental health	To be measured using the Patient Health Questionnaire-9 (PHQ-9) tool, which has been used in other settings in sub-Saharan Africa [30, 31], to identify adolescent mothers with depression symptoms

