## Abstract

**Introduction:**

Girls’ and women’s health as well as social and economic wellbeing are often negatively impacted by early childbearing. In many parts of Africa, adolescent girls who get pregnant often drop out of school, resulting in widening gender inequalities in schooling and economic participation. Few interventions have focused on education and economic empowerment of adolescent mothers in the region. We aim to conduct a pilot randomized controlled trial in Blantyre (Malawi) and Ouagadougou (Burkina Faso) to examine the acceptability and feasibility of three interventions in improving educational and health outcomes among adolescent mothers and to estimate the effect and cost-effectiveness of the three interventions in facilitating (re)entry into school or vocational training. We will also test the effect of the interventions on their sexual and reproductive health (SRH) and mental health.

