**Methods:**

We will conduct a baseline survey among adolescent mothers aged 10–19 years (N = 270, per site) enrolled following a household listing in select enumeration areas in each site. Adolescent mothers will be interviewed using a structured survey adapted from a previous survey on the lived experiences of pregnant and parenting adolescents in the two sites. Following the baseline survey, adolescent mothers will be individually randomly assigned to one of three study arms: arm one (adolescent mothers’ clubs only); arm two (adolescent mothers’ clubs + subsidized childcare), and arm three (adolescent mothers’ clubs + subsidized childcare + cash transfer). At endline, we will re-administer the structured survey and assess the average treatment effect across the three groups following intent-to-treat (ITT) analysis, comparing school or vocational training attendance during the intervention period. We will also compare baseline and endline measures of SRH and mental health outcomes. Between the baseline and endline survey, we will conduct a process evaluation to examine the acceptability and feasibility of the interventions and to track the implementation of the interventions.

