The three interventions we will assess are: (1) a cash transfer conditioned on (re)enrolment into school or vocational training and continued attendance; (2) subsidized child care; and (3) adolescent mothers’ clubs where adolescent mothers will receive life skills training covering nurturing childcare, SRH, and financial literacy. The choice of these interventions is informed by previous research highlighting financial constraints and lack of childcare as major barriers to school re-entry for parenting adolescents [3, 4]. These interventions also build on existing initiatives that provide a platform for scaling up should our research demonstrate their effectiveness. For example, the Government of Malawi runs the Social Cash Transfer Programme (SCTP), which provides ultra-poor and labor-constrained households an unconditional monthly transfer of about 7000 Malawian Kwacha (~ US$ 8.7) [16]. Currently, adolescent mothers are not targeted in the SCTP. The SCTP provides a framework for implementing cash transfers to parenting adolescents.

The specific objectives are to: (1) test the feasibility and acceptability of the interventions in the study contexts; (2) determine which combination(s) of interventions (cash transfer, subsidized child care, and adolescent mothers clubs) lead to the greatest increase in adolescent mothers’ re-entry into school or vocational training (primary outcome); (3) assess the effects of different combinations of the interventions on SRH and mental health outcomes among adolescent mothers (secondary outcomes); and (4) assess the cost-effectiveness of these interventions in increasing adolescent mothers’ re-entry into school or vocational training.

We hypothesize that these interventions will enhance adolescent mothers’ social, economic, health and education assets thereby allowing them to (re)enroll into school or vocational training. We also hypothesize that building these assets will lead to improved SRH and mental health outcomes for these mothers. Additionally, we hypothesize that combining the conditional cash transfer, subsidized child care and adolescent mothers’ club interventions is more effective in increasing re-entry into school and vocational training than adolescent mothers’ clubs only or combined adolescent mothers’ clubs and subsidized child care interventions.

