## Methods

### Study design

We will conduct a pilot RCT designed to estimate the effect of a conditional cash transfer and subsidized child care on adolescent mothers’ re-entry into school or vocation training. We also seek to examine the effects of the interventions on SRH outcomes and mental health as secondary outcomes, and to determine the most cost-effective interventions to increase adolescent mothers’ re-entry into school or vocational training. We will randomly assign adolescent mothers to one of three study arms. Adolescent mothers in all the arms will receive life skills training through adolescent mothers’ clubs. Adolescent mothers in arm two will also receive subsidized child care, while those in arm three will receive all three interventions. Comparing arm one (mothers’ clubs only) and arm two (mothers’ clubs + subsidized child care) will allow us to test the additional benefit of the subsidized child care. Comparing arms two and three (mothers’ clubs + subsidized child care + cash transfer) will also allow us to test the additional benefit of the cash transfer. Comparing arms one and three will allow us to test the combined benefit of the subsidized child care and cash transfers. The RCT design is summarized in Fig. 2.

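### The only comparison named for the secondary SRH and mental-health outcomes is baseline versus endline, which does not answer objective 3; and with clubs in every arm, the clubs' own effect cannot be estimated

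*Protocol article*

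**What the plan says.** Under Secondary outcomes, the article lists four SRH outcomes and one mental-health outcome (PHQ-9) and states: "We will compare baseline and endline measures of these outcomes". The Methods paragraph of the abstract first gives an intention-to-treat comparison across the three groups for school or vocational training attendance. It then adds, as a separate sentence: "We will also compare baseline and endline measures of SRH and mental health outcomes".

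The objectives in the Background set a different question for the same outcomes: "assess the effects of different combinations of the interventions on SRH and mental health outcomes among adolescent mothers".

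On design, the Study design section says "Adolescent mothers in all the arms will receive life skills training" through the clubs. It names three contrasts: arm 1 with arm 2 for childcare, arm 2 with arm 3 for cash, and a third described as "Comparing arms one and three will allow us to test the combined benefit of the subsidized child care and cash transfers".

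The abstract's aim is wider. It is to "estimate the effect and cost-effectiveness of the three interventions in facilitating (re)entry into school or vocational training", and the clubs are one of those three. The abstract also says that the effect of the interventions on SRH and mental health will be tested. For cost-effectiveness, Data processing and analysis describes the secondary effectiveness data as improvements in mental health and in SRH knowledge and practice.

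**The concern.** There are two linked problems.

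First, objective 3 is a between-arm question, while the comparison named for it is a before-after one. Over 12 months these outcomes can move for reasons unrelated to the interventions, and the article itself supplies several:

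- Mothers age, and their children, aged 1 to 3 years at entry, grow older.
- Currently pregnant girls are excluded at baseline only, which shifts the population behind contraceptive use by endline.
- The same questionnaire is given twice.
- Community dialogues run alongside the trial (Theoretical framework).

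Regression to the mean adds to this wherever attention falls on mothers with high baseline scores, for example on the PHQ-9. A before-after change cannot separate any of these from an intervention effect. A comparison of randomised arms can, because whatever is common to the arms cancels.

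Second, the clubs carry the SRH and mental-health content, yet no arm goes without them. Any statement about what the clubs achieve, or what they cost per unit of benefit, would have no counterfactual. At stake are objective 3, all five secondary outcomes, and the cost-effectiveness estimates built on them.

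**Working it through.** **Matching questions to comparisons**

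| Question | Comparison needed | What the article names |
|---|---|---|
| Effects of combinations on SRH and mental health (objective 3) | Between arms | Baseline versus endline |
| Added childcare | Arm 2 vs arm 1 | Listed in Study design, no outcome specified |
| Added cash | Arm 3 vs arm 2 | Listed in Study design, no outcome specified |
| Childcare and cash together | Arm 3 vs arm 1 | Listed in Study design, no outcome specified |
| Clubs | Clubs vs no clubs | No such arm |

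The last row is structural: clubs are constant across arms, so no analysis of these data isolates them.

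**How much a time trend could matter**

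The article gives no figure for the secondary outcomes, so there is none to reproduce. The following is illustration only.

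Inputs from the article: 90 per arm, 15% loss, two-sided 10% level. Completers per arm: 90 × 0.85 = 76.5. The 21% start is the regional contraceptive prevalence among adolescents quoted in the Background; it is not a figure for mothers at these sites. Assumed: a 10-point rise common to all arms, no intervention effect, baseline-endline correlation r = 0.5.

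*Binary outcome, 21% to 31%.*

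- Variances: 0.21 × 0.79 = 0.1659; 0.31 × 0.69 = 0.2139.
- SE of the paired change = √[(0.1659 + 0.2139 − 2 × 0.5 × √(0.1659 × 0.2139)) / n].
- One arm, n = 76: SE = 0.0502, z = 0.10 / 0.0502 = 1.99. Chance of significance ≈ Φ(1.99 − 1.645) ≈ 0.64.
- Three arms at one site, n = 228: z = 3.45. Chance ≈ Φ(3.45 − 1.645) ≈ 0.96.
- If the plan's design effect of 1.1 is applied, each z is divided by √1.1 = 1.049, giving 1.90 and 3.29, hence about 60% and 95%.

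*Continuous outcome, trend in SD units, r from 0.3 to 0.7.* SE = √[2(1 − r)/n], with n = 76.5 or 229.5, design effect ignored.

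| Common trend | One arm, before-after | Three arms pooled, before-after | Between-arm change |
|---|---|---|---|
| 0.1 SD | 19% to 31% | 36% to 62% | 10% |
| 0.2 SD | 44% to 73% | 82% to 99% | 10% |
| 0.3 SD | 72% to 96% | 99% to 100% | 10% |

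The last column is the nominal level, because a trend common to the arms drops out of their difference.

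**What the between-arm analysis can detect**

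Unadjusted at endline with 76.5 per arm, 80% power and two-sided 10%: (1.645 + 0.842) × √(2/76.5) = 0.40 SD. Adjusting for baseline multiplies the variance by 1 − r². At r = 0.5 that is 0.75, so the detectable difference becomes 0.40 × √0.75 ≈ 0.35 SD.

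**The case against.** A reader might infer that the investigators plan to credit before-after change to the clubs or the package, and that the randomised comparison will not be used for these outcomes. The article does not say so, and several places point the other way:

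- The contrasts in Study design are not limited to the primary outcome, and the same section speaks of examining the interventions' effects on SRH and mental health.
- The Covariates section refers to comparing effectiveness outcomes, in the plural, between arms.
- Data processing and analysis uses the baseline-and-endline phrase for enrolment inside an across-group intention-to-treat analysis. The secondary-outcome sentence could be shorthand for the same thing, for instance a difference in change.
- The model for each secondary outcome is normally left to an analysis plan, which is not shown.

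On the clubs, the quoted aim of estimating effect and cost-effectiveness concerns (re)entry, the primary outcome. No sentence claims a contrast of clubs against no clubs. The illustration also shows only that a real change over time is detectable; harm arises only if that change is called an effect.

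Most of this stands, and it reduces the point from a planned invalid inference to a mismatch that leaves room for one. It does not remove the mismatch. The two sentences that address the SRH and mental-health comparison directly both name baseline versus endline, and the abstract sets its sentence apart from the across-group analysis. The Covariates section names no outcome. No analysis plan, shown or not, can supply an arm without clubs.

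**Conclusion.** The point holds as a mismatch between objective 3 and the comparison named for it, together with a limit of the design that the summary wording does not acknowledge. Followed literally, the before-after comparison cannot answer objective 3. Whether it would be followed literally is a risk, not a stated intention.

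The 64% and 96% depend on the assumed 10-point trend and correlation of 0.5, and the tabulated ranges on other assumed values. The direction does not depend on them: any common trend raises the before-after rate above 10% and leaves the between-arm rate at 10%. That the clubs' effect and incremental cost-effectiveness are not estimable rests on no assumption beyond the stated arms.

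Severity is should-fix. These are secondary outcomes of a pilot, the data needed for the right comparison are already planned, and the between-arm comparison of the primary outcome is unaffected.

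**What to change.** 1. Replace the before-after sentence, in the outcomes section and in the abstract, with a statement on these lines: each secondary outcome at endline is compared between randomised arms (2 vs 1, 3 vs 2, 3 vs 1), adjusted for its baseline value, within each site, or with a site term if sites are pooled. The sample of 270 is stated per site, so pooling should not be presumed.
2. Label within-arm change from baseline as descriptive.
3. Base the secondary cost-effectiveness estimates on between-arm differences, not on improvement over time.
4. Limit effect and cost-effectiveness claims to childcare, cash, and both, each added to clubs, and state that the effect of the clubs themselves is not estimable.

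The cost is wording only: both survey rounds are already planned and randomisation is unchanged. Two things are given up: any claim about the effect of the clubs, and the apparent sensitivity of a before-after test. The randomised comparison would detect differences of roughly 0.35 to 0.40 SD under the assumptions above, and the report should say so.

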### Outcomes

#### Primary outcome

The primary outcome of this study is (re)entry or (re)enrolment in school or vocational training. At baseline, all participants will respond to a question on current school and vocational training enrolment and their intention to return to school or vocational training. At endline, participants will be asked whether they have attended school or vocation training at any time after the baseline. The primary outcome will be a binary variable coded 1 “Yes” or 0 “No” indicating whether or not the participant was enrolled in school or vocation training during the 12-month long intervention period.

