### Sample size and sample selection

Aside from using the pilot study to assess the feasibility and implementation of the intervention, we also aim to ensure that the pilot study provides us with preliminary data to accurately estimate the sample size for a fully-fledged intervention study in the future. That is, we expect the pilot data to enable accurate estimation for the within-group variance, intraclass correlation, and estimate of true effect size for a larger study. Thus, we approach the sample size estimation through a formal but naïve approach assuming there are two groups to compare (instead of three, and not accounting for multiplicity). We consider (re)enrolment in school or vocational training as the primary outcome. The sample size is estimated using the following parameters: in the lived experiences survey implemented in Malawi, the proportion of pregnant or parenting adolescents who were currently out of school was 94%. In a study conducted by the Population Council in Kenya, the proportion of adolescent mothers re-entering school following an intervention comprising policy dialogue, values clarification, and advocacy ranged from 10 to 16% [32]. Given that our proposed intervention addresses the key barriers to school re-entry identified in the Population Council study, we expect a higher rate of re-entry. For this study, we shall assume that the intervention, at the minimum, will achieve a 15% absolute reduction in the proportion of adolescents not in school. The minimum total required sample size for detecting this difference between two groups for a two-sided level of significance of 10%, and statistical power of 80%, can be computed as:$$n=\frac{{[{Z}_{1-\frac{\alpha }{2}}\sqrt{2\overline{pq} }+{Z}_{1-\beta }\sqrt{{p}_{1}\left(1-{p}_{1}\right)+{p}_{2}\left(1-{p}_{2}\right)}]}^{2}}{{({p}_{1}-{p}_{2})}^{2}}$$$${p}_{1}$$ is the proportion of pregnant or parenting adolescents who will be out of school in the intervention groups; $${p}_{2}$$ is the proportion for the arm receiving only the mothers club.; $$n$$ is minimum sample size per arm;$$\overline{p }=\frac{{p}_{1}+{p}_{2}}{2}$$, and$$\overline{q }=1-\overline{p }$$. Assuming a refusal or non-consent or attrition rate of 15% and a design effect of 1.1 due to possible clustering of adolescents from the same enumeration area (EA), the required sample size for detecting a difference between the control arm (group receiving only mother club membership) and one intervention arm is 90 adolescents per arm. In this pilot study with three arms, a total sample size of 270 adolescent mothers is needed.

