### Data processing and analysis

Outcomes will be measured pre-randomization (at baseline) and at the end of the 12-month intervention period (endline). Quantitative data will be collected on Android-based tablets programmed using SurveyCTO. The data will be synchronized to a password protected server. The data will then be transferred to Stata for further cleaning and analyses.

At the endline, we will estimate the average treatment effect across the three groups using intent-to-treat (ITT) analysis, comparing school/vocational training enrolment at baseline and endline. Primary analyses will be unadjusted. We will also compute adjusted effects (controlling for covariates) to account for differential attrition or any differences at baseline. Drawing on financial records detailing the cost of the interventions (cash transfers, childcare vouchers, and cost of running the mothers’ clubs), we will conduct cost-effectiveness analyses of the interventions. The cost per (re)enrolled adolescent mother will be the primary measure of the cost-effectiveness of the interventions. This costing data per adolescent mother will be further combined with secondary effectiveness data to calculate additional cost-effectiveness estimates of the interventions. Secondary effectiveness data will be measured through improvements in mental health of adolescent mothers and improved knowledge and uptake of SRH practices.

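### Table 1 words the only mental-health outcome as PHQ-9 case-finding and never names the total score; analysed as worded, it would have less power than the score already collected

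*Protocol article*

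**What the plan says.** The third specific objective, in the Background, is to "assess the effects of different combinations of the interventions on SRH and mental health outcomes among adolescent mothers (secondary outcomes"). Table 1 (Secondary outcomes) gives the mental-health domain a single row, measured with the PHQ-9 "to identify adolescent mothers with depression symptoms". The text introducing the table adds: "We will compare baseline and endline measures of these outcomes". Under Data processing and analysis, the secondary cost-effectiveness estimates depend on the same outcome: "Secondary effectiveness data will be measured through improvements in mental health of adolescent mothers".

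The article does not say whether the outcome is the PHQ-9 total or the share of mothers above a cut-off, and it prints no cut-off. The Covariates section lists sociodemographic, family and neighbourhood characteristics, but not the baseline PHQ-9. Data processing and analysis makes the primary analyses unadjusted and computes covariate-adjusted effects alongside them.

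**The concern.** The PHQ-9 gives an ordered symptom score. The one use stated for it is to pick out the mothers with symptoms, and the natural summary of that is a proportion. A case indicator registers change only in mothers who cross the cut-off. A mother whose symptoms ease while she stays above it, or stays below it, counts as unchanged.

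This fits the aims poorly. The third objective asks for effects on mental health, and the cost-effectiveness work needs improvement in it. The PHQ-9 is the only measure in one of the two secondary-outcome domains. With about 76 mothers per arm per site after the planned 15% loss (90 × 0.85 = 76.5), a case comparison could miss a benefit of childcare or cash that the score would show. That null would then pass into the cost-effectiveness estimates. If the score is what is meant, the table does not say so, and the choice between score and proportion stays open until the data are in.

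**Working it through.** **The plan's own figure.** The article states no power or sample size for the PHQ-9, so there is none to reproduce. Its 90 per arm is for (re)enrolment and serves here only as the planned enrolment. As an aside, the printed formula with 94% v 79% gives 63.1 per arm, and 63.1 × 1.1 / 0.85 = 81.7, not 90. A 15% relative reduction (94% to 79.9%) gives 69.5, and 69.5 × 1.1 / 0.85 = 90.0. The check below does not depend on which was meant.

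**Inputs from Sample size and sample selection.** 90 per arm per site, 15% loss, design effect 1.1, two-sided 10% alpha (z = 1.645). The alpha is stated there for the primary outcome and is borrowed here.

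Effective n per arm per site = 90 × 0.85 / 1.1 = 69.5. With both sites pooled it is 139.1.

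**Assumptions not in the article.** A normal PHQ-9 score, a between-arm shift d of 0.2 to 0.5 SD, and comparator case prevalence p₂ of 10% to 50%.

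**Formulas.**
- Score: power = Φ(d / √(2/n) − 1.645).
- Case indicator: p₁ = Φ(Φ⁻¹(p₂) − d), then the article's two-proportion formula solved for power: Φ{[|p₁ − p₂|√n − 1.645√(2p̄q̄)] / √[p₁(1 − p₁) + p₂(1 − p₂)]}.

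**Example, d = 0.4 and p₂ = 20%, by site.**
- Score: 0.4 / √(2/69.5) = 2.36, and 2.36 − 1.645 = 0.71, so power is 76%.
- Case: p₁ = Φ(−0.842 − 0.4) = 10.7%. The numerator is 0.093 × 8.34 − 1.645 × 0.510 = −0.065. Dividing by 0.506 gives −0.13, so power is 45%.
- Loss: 31 points.

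**Results by site (n = 69.5).**

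| d (SD) | Score power | Case power, p₂ = 10% | Case power, p₂ = 50% | Loss (points) |
|---|---|---|---|---|
| 0.2 | 32% | 16% | 24% | 8.2 to 16.1 |
| 0.3 | 55% | 24% | 40% | 14.7 to 30.8 |
| 0.4 | 76% | 33% | 58% | 17.8 to 42.9 |
| 0.5 | 90% | 43% | 75% | 15.6 to 47.8 |

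**Both sites pooled (n = 139.1).** Over the same grid the loss runs from 4.5 points (d = 0.5, p₂ = 50%: 99.4% v 95.0%) to 42.5 points (d = 0.4, p₂ = 10%: 95.5% v 53.0%).

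**Sensitivity.**
- At a 5% alpha the by-site range is 6.5 to 53.2 points.
- With 76.5 per arm (no design effect) and 10% alpha it is 8.8 to 47.2.
- With all 90 per arm and 10% alpha it is 10.0 to 45.4.
- Normality does not drive the direction. Simulated skewed negative-binomial scores (70 per arm, comparator prevalence 15% to 32%, mean reduction 25% to 30%) favoured the score by 14 to 21 points.

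**Baseline adjustment.** If baseline and endline scores correlate at 0.4 (assumed), the standard error shrinks by √(1 − 0.4²) = 0.917. By-site score power rises from 55%, 76% and 90% to 61%, 82% and 94% for d = 0.3, 0.4 and 0.5.

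**The case against.** The strongest reply is that the article never fixes a dichotomy. The row is titled mental health, not depression prevalence, and the phrase about identifying mothers may only describe what the tool is for. Where a binary outcome is meant, the article says so: "The primary outcome will be a binary variable coded 1 “Yes” or 0 “No". The wording on comparing measures and on improvements fits a score as well as a proportion. No row of Table 1 gives scoring rules, and a condensed article may leave them to a full protocol or an analysis plan that is not shown. This is also one of five secondary outcomes in a pilot sized only on (re)enrolment.

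Much of this stands. A reader might infer that the plan has chosen a yes/no endpoint and thrown the score away. The text does not support that. A reader might also take a power loss as a property of this trial. It is not, because the effect size and the prevalence are both assumed.

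What the reply does not remove is the wording. The only stated purpose of the measurement is case identification, and no other sentence names the score. Someone following Table 1 literally would compare proportions. The point therefore concerns what the article says, and does not rest on a missing scoring rule.

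**Conclusion.** The point holds in conditional form. Table 1 describes the PHQ-9 in case-finding terms, the total score is not named as the endpoint, and its baseline value is not among the covariates. If the outcome is analysed as case or non-case, power falls in every scenario examined. Under the stated assumptions the fall is about 8 to 48 points by site and about 4.5 to 42.5 points pooled. The direction is secure; the size is not, since the article supplies neither a PHQ-9 prevalence nor an effect. The weight is moderate: this is a secondary outcome for which the trial claims no power, but it is the sole mental-health measure and it feeds the cost-effectiveness work.

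**What to change.** In Table 1 and in Data processing and analysis, define the mental-health outcome as the endline PHQ-9 total score. Compare it between arms (one v two, two v three, one v three), adjusted for the baseline PHQ-9 score, with robust standard errors, or with an ordinal model if the score is skewed. Use that between-arm difference as the mental-health effect in the secondary cost-effectiveness estimates. Keep the proportion with depression symptoms as a supportive result and state its cut-off.

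The cost is a line or two of text. The PHQ-9 is already collected at baseline and endline, so no data or participants are added. The small downside is that a score difference means less to policy readers at first sight than a proportion; keeping the proportion as a supportive result covers that.
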